### Pilot study

We conducted a pilot study from February 1 – 25, 2008. The purpose of the pilot study was to test the feasibility and implementation of the trial. Specifically, we aimed to: 1) determine the referral rate from AVIVA Canada; 2) determine the participation rate; 3) test the administration of the baseline questionnaire; 4) ensure that the interventions can be delivered in a timely fashion and according to the protocol and 6) determine the 6- week follow-up rate.

The trial coordinators received 41 referrals during the pilot study for a referral rate of 1.6 calls per day. Of those, 36 were eligible and 12 consented to participate (participation rate = 33.3%). Our baseline and follow-up questionnaires were well received by participants. The six week follow-up rate was 58.3% (7/12). One participant dropped out of the study to receive care at another clinic and four participants could not be reached to complete the follow-up interview. The interventions were delivered without any difficulties.

### Protection of human subjects and assessment of safety

#### Protection of human subjects

The study protocol was approved by the University Health Network Research Ethics Board (07-0623-A).

#### Adverse events

We will measure the presence of adverse events that may be associated with the treatments at each follow-up interview. We defined adverse events as an unintended sign or symptom of the intervention. These include: increase in neck pain, stiffness, radiating pain/discomfort in arms, arm weakness, leg weakness, feeling tired, headache, dizziness, depression, anxiety or other physical discomfort. We will compute the intervention-specific incidence (95% CI) of each adverse event listed above. The intervention-specific cumulative number of visits will be used as the denominator. Any adverse event that is life-threatening or associated with significant disability will be reported to the University Health Network Research Ethics Board.

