**Inclusion criteria**
Diagnosed with Grade I or Grade II WAD
Report an average neck pain since the accident of at least 3 on a 0–10 "Numerical Rating Scale" (NRS)
Able to give written informed consent and complete interviews in English (translators will be available to assist the participant if she/he experiences difficulty understanding specific items on the questionnaire)
Make an insurance claim for physical injury and enroll in trial within 21 days of the traffic collision

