#### Acute-subacute phase

During the first six weeks post-injury, care will be delivered by physiotherapists, and if necessary kinesiologists and massage therapists. The care consists of: 1) reassurance; 2) education; 3) home exercises, 4) physiotherapy modalities to reduce pain and 5) massage therapy. A maximum of nine treatments (including massage therapy) during the first three weeks post-collision and an additional eight sessions (including massage therapy) between the third and sixth week post-collision will be allowed. The type and frequency of treatment will be prescribed by the physiotherapist based on her/his assessment. During this phase, the physiotherapist may recommend an "in-home" or "job site" functional assessment. Finally, the physiotherapist will refer the participant to a Multidisciplinary Evaluation if she/he is not progressing as expected.

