### Pre-approved framework guideline for Grade I and II Whiplash Associated Disorders (PAF)

The PAF is a clinical management guideline that focuses on the provision of interventions to manage pain and disability through functional restoration.[20] Its use is mandated in Ontario for patients with Grade I and II WAD.[20] The treatment will be provided under the supervision of a physiotherapist and includes: 1) reassurance; 2) education; 3) home exercises, and 4) encouragement to resume normal activities of daily living. Additionally, the physiotherapist may prescribe the following interventions: 1) exercise and functional activities; 2) mobilization and manipulation; 3) pain management modalities (including massage therapy); and 4) coping skills education. The frequency and number of visits is based on the clinical judgment of the physiotherapist but cannot exceed 10 visits within the first three weeks and nine visits three to six weeks post-collision.

Participants with significant functional limitations will be eligible for a functional assessment of their home, work or school environment. Based on the assessment, occupational therapists will develop an intervention that may include: 1) recommendation to use aids or devices; 2) minor modifications at the work, home, or school environment; 3) instructions on adaptive strategies or alternate approaches to fulfill functional tasks; and 4) specific functional activities to increase tolerance.

Participants who report significant improvement in the first six weeks of care, but who have not recovered, can receive up to four additional treatments over a two-week period. Participants who have not recovered will be re-evaluated and a new plan of management will be developed by the physiotherapist in charge of the care.

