### Data collection and follow-up

Table 2 summarizes the data to be collected during the trial. We will follow-up participants at six weeks, and three, six, nine and 12 months post-injury. All follow-up interviews will be conducted by a research assistant either in person at the study clinic or by telephone. The study research assistant will be blind to the treatment allocation and to the baseline characteristics of participants. However, because most outcomes are self-reported by the participants, the research assistant will not be blind to their outcomes status.

**Table 2 T2:** Measures used at baseline and follow-up interviews

**Measures**	**Baseline**	**6 Weeks**	**3 Months**	**6 Months**	**9 Months**	**12 Months**
Accident information	x					

Past history of neck pain and whiplash	x					

Numerical rating scale	x	x	x	x	x	x

Health care after accident	x					

Comorbidity questionnaire	x					

Acute 36-item short-form health survey (V2)	x	x	x	x	x	x

Work status	x	x	x	x	x	x

Expectation of recovery	x	x	x	x	x	x

Whiplash disability questionnaire	x	x	x	x	x	x

Center for epidemiological studies-depression scale (CES-D)	x	x	x	x	x	x

Vanderbilt pain management inventory	x	x		x		

Health state question	x	x	x	x	x	x

Socio-demographic characteristics	x					

Whether a lawyer or paralegal is involved in the claim	x	x	x	x	x	x

Global perceived recovery question	x	x	x	x	x	x

Satisfaction with care and treatment outcome		x	x	x	x	x

Co-interventions		x	x	x	x	x

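### Adverse events are counted from interviews but divided by all visits in the arm, so as written the rates are understated when participants miss interviews

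*Protocol article*

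**What the plan says.** Under Adverse events, the Protocol article gives one method of collection: "We will measure the presence of adverse events that may be associated with the treatments at each follow-up interview". It then plans an incidence with 95% confidence interval for each listed event in each arm, using the arm's cumulative number of visits as the denominator. The abstract lists a between-group comparison of adverse event rates among the secondary analyses.

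The interview dates are under Data collection and follow-up: "We will follow-up participants at six weeks, and three, six, nine and 12 months post-injury". The Sample size section assumes 30% loss to follow-up per arm. The Pilot study section reports: "The six week follow-up rate was 58.3% (7/12). One participant dropped out of the study to receive care at another clinic"; a further four could not be reached.

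On serious events the Adverse events section adds: "Any adverse event that is life-threatening or associated with significant disability will be reported to the University Health Network Research Ethics Board". It gives no route or time limit for this, and it does not tie the duty to the interviews.

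**The concern.** Numerator and denominator come from different sources. Events come from participants who complete an interview. Visits accrue to everyone treated in the arm, and nothing in the section limits them to those interviewed. A participant who attends sessions and then misses the interviews adds visits but no events.

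Two things are at stake. Each arm's rate is too low by an amount that depends on its loss. The comparison between arms is also distorted if loss differs, or if those lost had relatively more visits in one arm than in another. The number of visits depends on the program, so equal distortion across arms cannot be taken for granted.

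A lesser concern is timing. The first scheduled question about adverse events comes six weeks after injury, when the acute treatment period of the two rehabilitation arms is ending.

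**Working it through.** **Inputs from the article.** Planned loss 30% per arm, 148 participants per arm (Sample size). Pilot six-week follow-up 7/12 (Pilot study). Interviews timed from injury (Data collection and follow-up). Enrolment limit: "Make an insurance claim for physical injury and enroll in trial within 21 days of the traffic collision" (Inclusion criteria). Session caps: "A maximum of nine treatments (including massage therapy) during the first three weeks post-collision and an additional eight sessions" between the third and sixth week in the Soft Tissue Injury Care Model; in the PAF arm, visits "cannot exceed 10 visits within the first three weeks and nine visits three to six weeks post-collision".

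**Assumed.** v, the visits of a non-interviewed participant relative to an interviewed one, ranges from 0.5 to 1.5. Risk per visit is the same in both groups. m is the share of participants whose visits no interview covers.

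**Pilot figure reproduced.** 7/12 = 58.3%, as stated. Missed: 5/12 = 41.7%, exact 95% CI 15% to 72%. If the true loss were 30%, the chance of 5 or more missed out of 12 is 0.28, so the pilot does not contradict the planning figure.

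**Dilution of the rate.** Reported rate / true rate = (1 − m) / [(1 − m) + m·v].

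| m | v = 0.5 | v = 1 | v = 1.5 |
|---|---|---|---|
| 0.30 (planned loss) | 0.70/0.85 = 0.82 | 0.70/1.00 = 0.70 | 0.70/1.15 = 0.61 |
| 0.417 (pilot, six weeks) | 0.583/0.792 = 0.74 | 0.583/1.000 = 0.58 | 0.583/1.208 = 0.48 |

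At 30% loss, about 0.30 × 148 = 44 participants per arm would add visits without events.

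**Effect on the comparison, with no true difference between arms.**
- Loss 30% in one arm and 42% in another, v = 1: apparent rate ratio 0.70/0.58 = 1.21.
- Loss 30% in both arms, v = 0.5 in one and 1.5 in the other: 0.82/0.61 = 1.35.

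These are illustrations; the article gives no loss or visit figures by arm.

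**If the visits of non-interviewed participants are left out.** The term m·v disappears and the ratio is (1 − m)/(1 − m) = 1. What remains is selection, if risk per visit differs between those interviewed and those not.

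**Timing.** Six weeks is 42 days. With enrolment on days 0 to 21, the first interview falls 42 − 21 = 21 to 42 days, or 3 to 6 weeks, after enrolment. By then a participant may have had up to 9 + 8 = 17 sessions (Soft Tissue Injury Care Model) or 10 + 9 = 19 (PAF). The caps run from the collision, so these totals apply only to early enrolment. In the PAF arm, participants who have improved but not recovered "can receive up to four additional treatments over a two-week period", which can also end before the three-month interview. A full five-week interdisciplinary program that starts at week 6 ends at week 11, before that interview at about week 13. One that starts after about week 8 is still running then.

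**The case against.** The strongest reply is that the article does not say how non-interviewed participants enter the analysis, and that an unseen analysis plan may exclude their visits. If so, the dilution vanishes. But the denominator is a stated rule, and as written it takes all the arm's visits.

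A second reply is that 30% is a loss figure for the whole trial. Someone lost late has already been asked about the early, visit-heavy weeks, and a missed six-week interview may be made good at a later one. This stands: m may be below 30%, and the understatement correspondingly smaller.

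A third is that uniform questioning by a blinded interviewer is a sound way to compare mostly minor symptoms across arms. This also stands, and the fix keeps it.

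A reader might infer more than the text supports:
- **That serious harm will never be found, or that the ethics-board duty cannot be met.** The reporting sentence is not tied to interviews. Clinicians see participants during care, and physician-arm participants are told to get in touch if their complaint persists or worsens. Notification by clinicians, timelines and seriousness lists are commonly left to the full protocol.
- **That interviews always come after each intensive treatment phase.** For interdisciplinary rehabilitation this depends on its start date, which is not fixed.
- **That 42% is the expected loss in the main trial.** It is one time point in 12 people, and one of the five missed was a dropout rather than unreachable.
- **That those lost are the ones most likely to have been harmed.** Nothing in the article shows this.

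**Conclusion.** The mismatch is real and should be corrected. Events are collected by interview and divided by all visits in the arm, so as written the rates are understated when interviews are missed. At the planned 30% loss the reported rate is about 70% of the true rate, with a range of 61% to 82%. This assumes equal risk per visit, relative visits of 1 (range 1.5 to 0.5), and that 30% also describes the share of participants whose visits no interview covers. Unequal loss or visits would bias the comparison between arms, in a direction that cannot be known in advance.

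The timing point is secondary and conditional. The only collection route described starts 3 to 6 weeks after enrolment. Whether a faster route exists for serious events cannot be settled from the article.

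**What to change.** 1. Count in the denominator only visits in periods covered by a completed interview.
2. Report by arm the number of participants, and their visits, without interview data.
3. Record the reason for each withdrawal or failed contact, including possible harm where known.
4. Add a sensitivity bound that assigns non-interviewed participants a range of event rates per visit. A rate of zero reproduces the calculation as written; the upper end should be a stated multiple of the interviewed rate.
5. Unless the full protocol already does so, have existing clinic staff and trial coordinators notify the trial office of events reportable to the ethics board when they learn of them. Keep these reports out of the between-arm comparison of non-serious events, because arms with more visits have more chances to report.

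The cost is small: visits must be dated so that they can be matched to interview periods, the analysis gains one table, and staff need a short form and an instruction. The drawback is that the restricted rate describes interviewed participants only, which is why the bound should accompany it.

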**Methods and Design:**

We designed a pragmatic randomized clinical trial. A total of 444 participants (148 in each of three arms) who reside in Southern Ontario, Canada will be recruited from a large insurer. We will include individuals who are 18 years of age or older and who are diagnosed with Grade I or II Whiplash-associated Disorders. Participants will be randomized to physician-based education and activation or one of two rehabilitation programs of care currently in use in Ontario. Our primary outcome, self-rated global recovery and all secondary outcomes (neck pain intensity, whiplash disability, health-related quality of life, depressive symptomatology and satisfaction with care) will be measured at baseline by a trial coordinator and at 6 weeks, 3, 6, 9 and 12 months follow-up by an interviewer who is blind to the participants' baseline characteristics and treatment allocation. We will also collect information on general health status, other injuries, comorbidities, expectation of recovery, work status, pain coping, legal representation, and co-interventions. The primary intention-to-treat analysis will compare time to recovery between the three interventions. This trial will have 90% power at an alpha of 0.05 to detect a 20% difference in the rate of perceived recovery at one year. Secondary analyses will compare the health outcomes, rate of recurrence and the rate of adverse events between intervention groups.

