### Secondary outcomes

To analyze the continuous secondary outcomes (neck pain intensity, whiplash disability, health-related quality of life, depressive symptomatology, satisfaction with care), we will first compute the intervention-specific mean, standard deviation and median at each follow-up interval. Second, we will build ordinary least-square (OLS) models using generalized estimating equation (GEE) to account for the autocorrelation present in the outcomes.[51] Third, we will test whether the intervention effects are constant throughout the follow-up periods.[51] Fourth, we will test whether imbalances in the distribution of the baseline covariates confound the intervention effects. Covariates added to the crude linear model that change any of intervention regression coefficients by 10% percent or more will be retained as confounders in the adjusted models.[50] The intervention effects will be reported as the mean differences and 95% for each follow-up interval.

We will analyze time to claim closure using the Kaplan-Meier method and the Cox proportional hazards model as described above. Effectiveness will be reported as the HRR and 95% CI.

To analyze the recurrence rate, we will first compute the intervention-specific incidence (95% CI) of recurrence. Second, we will use Poisson regression and GEE to account for the autocorrelation present in the report of self-perceived recovery.[51] In the Poisson model, the number of recurrences will be used as the outcome variable. Third, we will test whether imbalances in the distribution of the baseline covariates confound the intervention effects. Covariates added to the crude Poisson model that change any of intervention regression coefficients by 10% percent or more will be retained as confounders in the models.[50] We will present the intervention effects as relative risks (RR) and 95% CI.

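### Adverse events are recorded as present at each of five interviews and summarised as an incidence per visit, so one lasting symptom can be counted up to five times; participants should be the unit

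*Protocol article*

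**What the plan says.** The Adverse events section fixes four things.

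- **What is recorded and when:** "We will measure the presence of adverse events that may be associated with the treatments at each follow-up interview". Data collection and follow-up sets the schedule: "We will follow-up participants at six weeks, and three, six, nine and 12 months post-injury". That makes five interviews.
- **What qualifies:** "We defined adverse events as an unintended sign or symptom of the intervention". The listed types are "increase in neck pain, stiffness, radiating pain/discomfort in arms, arm weakness, leg weakness, feeling tired, headache, dizziness, depression, anxiety or other physical discomfort".
- **The summary measure:** "We will compute the intervention-specific incidence (95% CI) of each adverse event listed above".
- **The denominator:** "The intervention-specific cumulative number of visits will be used as the denominator".

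The section has no rule that an event must be new since the previous interview and no rule that a participant counts once per event type. It gives no method for the interval and does not say whether visits are treatment visits or interviews.

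The Abstract (Methods and Design) promises a comparison of arms: "Secondary analyses will compare the health outcomes, rate of recurrence and the rate of adverse events between intervention groups". For recurrence, which comes from the same interviews, the Secondary outcomes part of the Statistical analysis does provide for repeated reports: "Second, we will use Poisson regression and GEE to account for the autocorrelation present in the report of self-perceived recovery".

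**The concern.** Presence at an interview is prevalence-type information, whereas incidence means new occurrences. Joining the two without a rule for what counts as new leaves one natural reading: add up the reports and divide by visits. A visit denominator points the same way, since a count of people would normally be divided by people.

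Most of the listed events, such as stiffness, headache, tiredness, dizziness, depression and anxiety, can last from one interview to the next. If repeats count, two arms with the same number of people affected can show different rates only because symptoms last longer in one of them. To the extent that the counted symptoms follow recovery from the injury, that duration is something the arms are meant to change, and a slower-recovering arm could look more harmful with no extra person harmed. At stake is the between-arm safety comparison promised in the Abstract.

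**Working it through.** The article states no adverse event count, rate or interval width, so there is no figure to reproduce. The checks below are illustrations; inputs not in the document are marked as assumed.

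**1. Most reports one symptom can produce.** Five interviews give at most 5 reports per participant per event type.

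**2. Reports per affected participant.** Assumed: 20% have the symptom at week 6, there is no later onset, all five interviews are completed, and the symptom persists to the next interview with probability q. Then R(q) = 1 + q + q² + q³ + q⁴.

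**3. Spread of the count.** Let D be the number of reports from an affected participant, with E[D²] = Σ(2j − 1)q^(j−1) for j = 1 to 5. Per participant, with p = 0.2, the mean is pR and the variance is pE[D²] − (pR)². The true SD over the Poisson SD is the square root of variance/mean. For q = 0.8: R = 3.362 and E[D²] = 13.870, so the variance is 2.774 − 0.452 = 2.322 and the mean is 0.672; √(2.322/0.672) = 1.86. With 114 participants per arm (the article's number before its dropout allowance), 114 × 0.2 = 22.8 are affected.

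| q (assumed) | R(q) | Expected reports, 22.8 × R | SD / Poisson SD | Coverage of nominal 95% Poisson interval (2,000 simulated arms) |
|---|---|---|---|---|
| 0.3 | 1.43 | 32.5 | 1.24 | 87% |
| 0.5 | 1.94 | 44.2 | 1.51 | 81% |
| 0.7 | 2.77 | 63.2 | 1.76 | 74% |
| 0.8 | 3.36 | 76.6 | 1.86 | 70% |

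The normal approximation 2Φ(1.96/ratio) − 1 agrees: 88% at q = 0.3 and 71% at q = 0.8.

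A second simulation used 148 per arm, 20% at the first interview, 2% new onset per interval, and a binomial interval that treats interviews as independent. Its coverage was 79% at persistence 0.5 and 68% at 0.8. An interval clustered on participant gave about 94% in both cases. With almost no persistence (0.02), the naive interval covered about 96%, so the shortfall comes from persistence.

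**4. Effect on a comparison of raw counts.** With 20% affected in both arms, persistence 0.7 against 0.3 gives 2.773/1.425 = 1.95, and 0.7 against 0.5 gives 2.773/1.9375 = 1.43. These are ratios of report counts. They equal ratios of the planned incidence only if the visit denominators are equal.

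**5. Effect of the denominator.** Assume 30 of 148 participants affected (20.3%).

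- If visits are interviews (5 × 148 = 740): 30/740 = 4.1% when the symptom is present at one interview, 60/740 = 8.1% at two, and 150/740 = 20.3% at all five.
- If visits are treatment visits, numbers differ by design. The physician arm may end after the initial visit. The acute-subacute phase of the Soft Tissue Injury Care Model allows up to 9 + 8 = 17 sessions, before any interdisciplinary programme. The pre-approved framework allows up to 10 + 9 = 19 visits, plus up to four more treatments (23). With each person counted once, the result is 30/148 = 0.203 at one visit each, 30/(148 × 17) = 0.012 at 17, and 30/(148 × 23) = 0.009 at 23. With five reports each, one visit per person gives 150/148 = 1.01, which cannot be a proportion.

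The session limits are maxima, so actual contrasts may be smaller. Counting participants gives 30/148 = 20.3% in every case.

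**The case against.** The strongest reply is that this reads an error into a silence. Incidence ordinarily means new occurrences, and asking at every interview is a way of collecting events, not a rule for counting them. A condensed article may leave first-occurrence rules and interval methods to the full protocol or analysis plan, and not naming GEE in a short safety paragraph is no evidence of a naive interval. The definition also limits events to those of the intervention, and the first listed type is itself a change.

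Much of this stands, and it rules out several stronger readings that a reader might infer:

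- **That the figure measures symptom duration.** Even with repeats summed, it would mix onset and duration, and the article does not say that repeats are summed.
- **That the intervals are too narrow.** This follows only if repeats are counted and treated as independent; no interval method is stated.
- **That the last three interviews mostly record persistence after treatment.** The described phases add up to about 8 weeks (six plus two) or 11 weeks (six plus up to five). That leaves no time for the multidisciplinary evaluation, and the framework arm allows a new management plan with no stated end.
- **That the planned rate would differ 1.95-fold between arms.** That figure compares raw counts under assumed persistence.

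The reply does not remove the mismatch in what the article does fix: presence, at every interview, labelled incidence, divided by visits. Followed as written, these choices give reports per visit. A later plan that supplied a first-occurrence rule would still inherit the visit denominator.

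**Conclusion.** The point holds as a weakness in the stated method. As written, the adverse event figure allows one lasting symptom to count up to five times, can mix onset with duration, and uses a denominator that is neither persons nor person-time and differs by design between arms. Under the assumptions in the working, repeat counting gives 1.4 to 3.4 reports per affected participant. If reports are also treated as independent, nominal 95% coverage falls to roughly 87% to 70%. The onset and persistence values have no source in the document, and the visit denominator can move the result by more than repeat counting does.

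This concerns a secondary safety summary and leaves the primary analysis untouched. It is best treated as a cheap improvement; it does not show that the planned intervals are wrong.

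**What to change.** In the Adverse events section, replace the per-visit figure. For each listed event type, count a participant once, at the first interview where it is newly reported. Give the number and proportion of participants in each arm with at least one such event, with a participant-level 95% CI, and the between-arm difference or ratio that the Abstract promises. Put continuing and repeat reports in a separate table.

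If event counts are kept as the headline, count only onsets (absent at the previous interview) and analyse them with Poisson regression and GEE clustered on participant, as already planned for recurrence.

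The cost is a change of wording and a small recoding of data already to be collected. The small downside is that repeat episodes leave the headline figure and appear only in the separate table.

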#### Initial visit

The intervention includes reassurance, education about the favorable prognosis of WAD, encouragement to resume activities of daily living, recommendation to do home exercises (stretching) and, if indicated, prescribe pain relief modalities (heat/ice, acetaminophen or a Cox-2 selective non-steroidal anti-inflammatory drug (NSAID) or non-selective NSAID with or without gastroprotection). At the end of the initial visit, the physician will determine whether a follow-up appointment is necessary or if the participant should be discharged. The participant will be informed to contact the physician should their complaint persist or worsen.

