#### Follow-up visits

If follow-up visits are necessary, the participant will be re-assessed and the intervention described above will be repeated and adapted to the participant's status. Participants who have not recovered six weeks after the injury or have improved but require more care will be referred for a multidisciplinary evaluation and enter the interdisciplinary rehabilitation (described above under Soft Tissue Injury Care Model).

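### Adverse events are divided by treatment visits, which depend on the assigned arm, so the between-arm safety comparison is distorted by visit intensity, in a direction that the protocol does not determine

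*Protocol article*

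**What the plan says.** The Adverse events section describes both parts of the rate. On the numerator: "We will measure the presence of adverse events that may be associated with the treatments at each follow-up interview." On the denominator: "The intervention-specific cumulative number of visits will be used as the denominator." The result is an incidence with a 95% CI for each listed event in each arm. The abstract (Methods and Design) says that secondary analyses will compare the "rate of recurrence and the rate of adverse events between intervention groups".

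Interviews take place at 6 weeks and at 3, 6, 9 and 12 months in every arm (Data collection and follow-up). Treatment visits follow no common schedule:

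- Soft Tissue Injury Care Model, acute-subacute phase: "A maximum of nine treatments (including massage therapy) during the first three weeks post-collision and an additional eight sessions" up to week six.
- PAF: visits "cannot exceed 10 visits within the first three weeks and nine visits three to six weeks post-collision". Those improved but not recovered "can receive up to four additional treatments over a two-week period". For those not recovered there is then a new plan with no stated number of visits.
- Physician arm: after the initial visit, "the physician will determine whether a follow-up appointment is necessary or if the participant should be discharged". No cap or expected number is given. Later, "Participants who have not recovered six weeks after the injury or have improved but require more care will be referred for a multidisciplinary evaluation". From there they join the same interdisciplinary rehabilitation as the Soft Tissue arm, which can run daily for up to five weeks.

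No rate per participant or per unit of person-time is described.

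**The concern.** Numerator and denominator arise from different processes. Events are captured through interviews that are the same for everyone. The denominator counts treatment contacts, which the allocation itself sets. Two arms in which each participant runs the same risk will then show different rates merely because one delivers more visits.

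Three features add to the problem. First, visits depend on outcome: participants who do not recover receive more care in all three arms, so slow recovery enlarges the denominator and lowers the reported rate. Second, several listed events (headache, tiredness, depression, increased neck pain) can occur at any time, and exposure to home exercise or medication continues between visits. Third, someone who attends treatment but misses interviews adds to the denominator and nothing to the numerator. The sample size section assumes 30% loss to follow-up, and 7 of 12 pilot participants were followed at six weeks.

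What is at stake is the comparative safety statement. A patient choosing between programmes needs the risk per person, and the stated rule does not estimate it.

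**Working it through.** The article states no adverse-event rate and no expected visit count, so there is no figure to reproduce. The check asks what the stated rule returns when the risk per person is equal in all arms.

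**Reading of terms.** "Visits" is taken to mean treatment visits, because the article calls the research contacts interviews.

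**Inputs from the article**
- Soft Tissue ceiling in the first six weeks: 9 + 8 = 17.
- PAF ceiling in the first six weeks: 10 + 9 = 19, then up to 4 more.
- Physician arm: at least the initial visit.
- Planned participants per arm: 148.

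**Assumptions (not in the article)**
- Risk per person: 30% in every arm. It cancels from the ratios.
- u, share of the six-week ceilings used: 50% or 100% in the main cases.
- v, physician visits per participant: 2 in the main cases.
- f, share continuing to further care, the same in each arm: 0% to 50%.
- Interdisciplinary rehabilitation: 25 sessions (five weeks at five days a week).

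**Formula.** Rate per visit = (148 × risk) / (148 × mean visits). At equal risk,

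physician rate / rehabilitation rate = mean rehabilitation visits / mean physician visits.

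A value above 1 makes physician care look worse, and a value below 1 makes it look better. The true risk ratio is set at 1.

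**First six weeks (f = 0)**
- At the ceilings with v = 2, the rates per 100 visits are 30/17 = 1.76 (Soft Tissue), 30/19 = 1.58 (PAF) and 30/2 = 15.0 (physician). The ratios are 17/2 = 8.5 and 19/2 = 9.5.
- At half the ceilings with v = 2: 8.5/2 = 4.25 and 9.5/2 = 4.75.
- At a quarter of the ceilings with v = 4: 4.25/4 = 1.06 and 4.75/4 = 1.19, almost no distortion.

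**Whole pathway.** Mean visits are 17u + 25f (Soft Tissue), 19u + 4f (PAF) and v + 25f (physician). With u = 0.5 and v = 2:

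| f | Soft Tissue visits | PAF visits | Physician visits | Soft Tissue / physician | PAF / physician |
|---|---|---|---|---|---|
| 10% | 11.0 | 9.9 | 4.5 | 2.44 | 2.20 |
| 30% | 16.0 | 10.7 | 9.5 | 1.68 | 1.13 |
| 50% | 21.0 | 11.5 | 14.5 | 1.45 | 0.79 |

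**Where the PAF comparison reverses.** Setting 19u + 4f = v + 25f gives f = (19u − v)/21. With u = 0.5 and v = 2, f = 7.5/21 = 36%. With u = 0.25 and v = 2, f = 2.75/21 = 13%. With u = 1 and v = 2, f = 17/21 = 81%.

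**Per participant.** 148 × 0.30 = 44.4 and 44.4/148 = 30% in every arm, ratio 1.0.

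**The case against.** A reader might infer that the rehabilitation arms are bound to look several times safer. The article does not support that. The figures of 17 and 19 are ceilings, frequency is left to the physiotherapist, and physician visits are uncapped. Unrecovered physician-arm participants also move into up to five weeks of daily sessions, which narrows the gap and can reverse it against PAF. In the other direction, the open-ended new plan under PAF could add visits that the calculation leaves out. This part of the objection stands: neither a fixed size nor a fixed direction can be claimed.

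A reader might also infer that the numerator cannot rise with visits at all. That goes too far. An adverse event is defined as an unintended effect of the intervention, so a period with more sessions offers more chances for one to occur and be reported. Interview capture limits how closely the count can follow visits, but does not prevent it from rising. For harms tied to treatment contact, a rate per visit answers a legitimate question, though a different one from the risk per person.

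Finally, the Adverse events section itself plans only arm-specific incidences, the comparison is announced in the abstract, and safety is not among the listed objectives. Life-threatening or significantly disabling events go to the ethics board whatever the denominator. This limits the consequence. It does not rescue the comparison, because no rate per participant or person-time is described beside it.

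**Conclusion.** The point holds as a defect of a stated rule, not as an omission left to a fuller document. The denominator depends on the assigned arm and on non-recovery, so rates per visit do not compare risk per person between arms.

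Size and direction depend on realised visits, which the article does not give. Early on, the distortion probably favours the rehabilitation arms, by several-fold if physician visits are few and the ceilings are substantially used. Over the full pathway it shrinks under the assumptions shown and may change sign for PAF. Against the Soft Tissue arm the ratio stayed above 1 in every scenario run (1.01 to 17). All these figures rest on the assumed use of ceilings, physician visits, share continuing and 25 later sessions. A comparison whose bias can change direction with the care delivered cannot be read as comparative safety.

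The scope is the secondary safety comparison. The primary outcome is unaffected.

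**What to change.** Replace the denominator sentence so that the main between-arm safety comparison is per participant, by randomised arm:

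- the proportion reporting each event at each interview, among those interviewed;
- the proportion with at least one event over observed follow-up, or a rate per person-time, by a method that accounts for missed interviews. A simple count of those with any event by 12 months would understate risk where interviews are missed;
- risk differences (rate differences if person-time is used) with 95% CI.

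Keep events per visit only as a supplementary description, labelled as such, with the mean number of visits per arm beside it.

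The cost is a changed sentence and a little more analysis. Events are already to be recorded at each interview, so no new data and no change to the design are needed.
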